## Abstract

**Background:**

Previous research suggests that perceptions of peer substance use are associated with personal use. Specifically, overestimating use in the peer group is predictive of higher rates of personal substance use. ‘Social norms’-interventions are based on the premise that changing these misperceived social norms regarding substance use by providing feedback on actual norms is associated with a reduction in personal substance use. Studies conducted in the U.S.A. suggest that ‘social norms’-feedback is an effective strategy for reducing substance use among university students. It is unknown whether the effects of a ‘social norms’-feedback on substance use can be replicated in a sample of German university students. The objective of this article is to describe the study design and aims of the ‘INternet-based Social norms-Intervention for the prevention of substance use among Students’ (INSIST)-study, a cluster-controlled trial examining the effects of a web-based ‘social norms’- intervention in students enrolled at four intervention universities with those enrolled at four delayed intervention control universities. The INSIST-study is funded by the German Federal Ministry of Health.

**Methods/Design:**

Eight universities in four regions in Germany will take part in the study, four serving as intervention and four as delayed intervention control universities (randomly selected within a geographic region). Six hundred students will be recruited at each university and will be asked to complete a web-based survey assessing personal and perceived substance use/attitudes towards substance use at baseline. These data will be used to develop the web-based ‘social norms’-feedback tailored to gender and university. Three months after the baseline survey, students at intervention universities will receive the intervention. Two months after the launch of the intervention, students of all eight universities will be asked to complete the follow-up questionnaires to assess changes in perceptions of/attitudes toward peer substance use and rates of personal substance use.

**Discussion:**

This study is the first German cluster-controlled trial investigating the influence of a web-based ‘social norms’-intervention on perceptions of/attitudes towards substance use and substance use behavior in a large university student sample. This study will provide new information on the efficacy of this intervention strategy in the German university context.

**Trial registration:**

DRKS00007635 at the ‘German Clinical Trials Register’ (17.12.2014).

## Background

Licit and illicit substance use (i.e., using alcohol, tobacco, cannabis and other illicit substances) is considered a key public health concern among university students. In regard to licit substance use, findings of previous studies suggest that university students tend to consume more alcohol than young adults of similar ages who are not studying [1, 2]. While daily drinking is comparatively low (4 % reported consumption of alcoholic beverages every day during the last three months), heavy drinking is common among German university students [3]. Keller and colleagues [4] estimated a 62 % three month heavy drinking prevalence among German university students. In another study, 16 % of German university students reported that they practiced heavy drinking at least once per week [3]. In regard to illicit substance use, one study reported a lifetime prevalence of 40 % for cannabis use in a sample of 3307 German university students [5]. Because university students are more likely to engage in unhealthy or risky substance use, such as heavy drinking, they are at a particular risk for substance use-related consequences, such as vandalism or sexual violence [6].

Results of a literature review summarizing findings of 65 articles examining the role of students’ characteristics in relation to alcohol use at European campuses indicate that alcohol is mainly consumed during social gatherings and that social motives for drinking prevail in this population [7]. Substance use is perceived to be a normal part of students’ life and personally engaging in substance use is perceived to be an adequate behavior to match the norm of peer behavior and therefore maintain conformity with peers [8]. However, international research suggests that university students tend to overestimate both the perceived quantity (*descriptive norm*) [9–11] and perceived acceptability (*injunctive norm*) [12] of alcohol and other substances used by their peers.

Inaccurate perceptions can cause the individual to increase their own consumption in an attempt to match their personal behavior to the peer norm. Overestimations of peer licit [9, 10, 13] and illicit substance use [14–16] and associations with increased personal substance use among university students have been demonstrated in several previous studies [9, 13, 16].

Based on this observation, so called ‘social norms’-interventions were developed which aim to change university students’ perceptions of attitudes towards substance use among their peers and of peer substance use, using feedback [17]. Typically, participants of ‘social norms’-interventions are exposed to feedback contrasting their perception of substance use and attitudes towards use among their peers with data on actual use and attitudes in their peer group. Data on perceived attitudes and use, as well as actual attitudes and use, are assessed prior to the development of the feedback. Findings of ‘social norms’-intervention studies suggest that providing feedback on actual peer consumption rates to students leads to a reduction of social pressure on the individual and may consequently reduce personal substance use [18, 19]. ‘Social norms’-interventions have been delivered employing a mass media marketing approach [20], have targeted individuals [21] and have been implemented in group counselling sessions [22]. In more recently developed interventions, ‘social norms’-feedback was delivered via the internet [18, 19]. One advantage of web-based interventions is that the messages can be personalized. Feedback on actual peer norms can be based on national norms [22], behavior and attitudes of university students at a person’s university [23] and can also be presented gender neutral [24] or stratified for same-gender peers [25].

To date, ‘social norms’-intervention research has largely been restricted to the North-American college system and little is known about how perceptions of peer use influence personal substance use in European students [8]. The ‘Social Norms Intervention for the prevention of Polydrug usE’ (SNIPE) study was the first multi-national study that aimed to develop an online ‘social norms’-intervention portal which was implemented in seven European countries [26]. In the present study, this intervention will be translated and adapted to the German university context. The main aim of the study is to investigate whether participation in this intervention leads to greater changes in misperceived social norms and a more pronounced reduction of licit and illicit substance use among German university students enrolled at four intervention universities compared to students enrolled at four delayed intervention control universities. This cluster-controlled trial is funded by the German Federal Ministry of Health.

## Methods

### Study aims

The primary objectives of the INSIST (‘INternet-based Social norms-Intervention for the prevention of substance use among Students’)-study are to evaluate (I) whether misperceptions of peer substance use are reduced as a consequence of participating in the intervention and (II) whether students participating in the intervention report lower rates of substance use at follow-up than those not participating in the intervention. Differences between the estimates (norms and use of substances) of students of the intervention and the control group are used as indicators to measure possible intervention effects.

Secondary objectives of the INSIST-study include:(i)The detailed assessment of self-reported consumption rates of licit and illicit substances in a large sample of German university students;(ii)the adaption of an internationally implemented ‘social norms’-intervention to the needs of German university students using qualitative results of focus group discussions with university students.

### Participants and procedures

Ethical approval was obtained from institutional review boards of all participating universities (Research and Ethics Committee of the Department of Life Sciences, HAW Hamburg; MHH Ethics Commission, Hannover Medical School; Ethics Commission of the University of Münster provided approval for the study site at the University of Bielefeld; Ethics Commission of the Heinrich Heine University Düsseldorf; Ethics Commission of the Martin Luther University Halle-Wittenberg; Ethics Commission of the Technical University Dresden; Medical Ethics Commission II of Mannheim University provided approval for the study site at Heidelberg University and Mannheim University). In addition, issues regarding data protection were monitored by the local data protection agency in the city state of Bremen. Eight universities in four regions will participate in the study (Hamburg University of Applied Sciences, Hannover Medical School, University of Bielefeld, Heinrich Heine University Düsseldorf, Martin Luther University Halle-Wittenberg, Technical University Dresden, Heidelberg University, and Mannheim University). In each region, one university will serve as the intervention site and one as the comparison site. Within a geographical area intervention and control universities will be determined by random selection. However, intervention and control universities in each of the four regions will be located in different cities. Social contacts between students of these two universities are expected to be minimal, as well as the likelihood of cross-contamination of intervention effects.

Students of all participating universities will be invited to participate in the INSIST-study. For the recruitment of students, an overall recruitment strategy across all universities will be employed. At each university, one local student will be employed by the study who will be in charge of recruitment at the university. We expect that these students will be familiar with structures and processes at their universities which may facilitate recruitment. Students will be recruited to the study via email, the universities’ websites, intranet or student e-learning platforms. Additional public recruitment channels will include local newspaper articles, local radio broadcasts, and student newsletters. Moreover, students will be personally invited to participate in the study in seminars by lecturers. Posters and flyers promoting the study will be posted at universities and Facebook will be used to publicize the study.

To participate in the INSIST-study, students will be asked to firstly register for the study via email. The email will contain a hyperlink to the survey website where students can enter their email-address and choose their respective university and gender (female, male, or other). This information is necessary to create the individualized university- and gender-specific’social norms’-feedback. Students will be informed on the study website that they can withdraw from the study at any time. If they register and choose to take part in the study, students will receive an email with information regarding the date the baseline survey is available. After the survey is launched, registered students will be informed via email that they can fill out the baseline questionnaire.

### Sample size

The sample size calculation is based on the prevalence for heavy drinking reported in a previous study conducted in Germany with 3307 students [5]. In total, we aim to reach 4800 students at baseline, 600 students at each participating university. We assume a 40 % loss to follow-up five months post-baseline. The sample size will allow an estimation of a difference in the rate of heavy drinking between the intervention and control sites (at follow-up), corresponding to an effect size of 0.2 at the level of p < .05 with 81 % power.

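### The stated 81% power cannot be reproduced from the inputs printed beside it, and with four universities per arm an unadjusted two-sided comparison on 6 df reaches it only if the ICC is about 0.004 or less

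*Protocol article*

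**What the plan says.** The protocol article's Sample size section sets the recruitment target and attrition: "In total, we aim to reach 4800 students at baseline, 600 students at each participating university. We assume a 40 % loss to follow-up". It names heavy drinking at follow-up, intervention sites against control sites, as the quantity being powered, and describes the detectable difference as "corresponding to an effect size of 0.2 at the level of p < .05 with 81 % power". The base rate is not printed; it is taken from a cited survey: "The sample size calculation is based on the prevalence for heavy drinking reported in a previous study conducted in Germany with 3307 students". The section does not say whether 0.2 is a standardised difference, a relative reduction or something else, whether the test is one- or two-sided, or whether clustering entered the calculation.

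The design is clustered. There are eight universities in four regions, one per arm in each region, and allocation is of whole universities: "Within a geographical area intervention and control universities will be determined by random selection".

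**The concern.** A power statement that prints its sample size, attrition, significance level and effect size should be reproducible from them. This one is not, under the usual meaning of an effect size of 0.2. The planned number is about 3.6 times what 81% would need for independent students, so rounding cannot explain the gap.

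The direction of the gap suggests that an allowance for clustering may have been made without being reported. If that was done with a normal-theory design effect, the result is still too favourable, because only eight universities inform the between-university variance.

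This is the only power figure in the article. If follow-up shows no difference, readers will use it to judge whether an effect of 0.2 has been reasonably excluded, so the figure needs a basis that can be checked.

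**Working it through.** **Inputs.** From Sample size: 4800 students, 600 per university, 40% loss, effect 0.2, 5% level, power 81%. From Participants and procedures: eight universities, four per arm. Assumed because not stated: two-sided test, 0.2 as a standardised effect (Cohen's d or h), and the ICC.

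**Completers.** 4800 × 0.6 = 2880, so 1440 per arm and 360 per university.

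**Attempt to reproduce 81%, independent students.**
- Power = Φ(0.2 × √(1440/2) − 1.96) = Φ(5.37 − 1.96) = Φ(3.41) = 99.97%.
- Number per arm for 81%: 2 × (1.96 + 0.878)² / 0.2² = 403.
- Effect detectable with 81% power at 1440 per arm: (1.96 + 0.878) × √(2/1440) = 0.106.
- With 0.2 as Cohen's h, power is 99.96% to 99.97% at every base rate tried from 10% to 62%.
- One-sided testing gives 99.99%. A single pair of universities with 360 completers each gives 76.5% two-sided or 85.0% one-sided. None of these is 81%.

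**What does return about 81%.**
- A design effect: 1440/403 = 3.57, so ICC = (3.57 − 1)/359 = 0.0072, using normal quantiles. A one-sided test needs 319 per arm, and the implied ICC is (1440/319 − 1)/359 = 0.0098.
- A different metric with no clustering: a risk ratio of 0.8 gives 79.8% at a 20% base rate and 81.0% at 20.5%. An odds ratio of 0.8 gives 80.0% at 35%, 82.5% at 40% and 83.6% at 62%.

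**Power with eight universities.** Design effect DE = 1 + 359 × ICC. Noncentrality = 0.2 × √(720/DE). Two-sided 5%, noncentral t. The 6-df column is an unpaired, unadjusted comparison of follow-up rates. The 3-df column treats the four regions as pairs but credits no variance removed by pairing.

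| ICC (assumed) | DE | Normal theory | t, 6 df | t, 3 df |
|---|---|---|---|---|
| 0 | 1.00 | 99.97% | 99.3% | 93% |
| 0.002 | 1.72 | 98% | 92% | 77% |
| 0.004 | 2.44 | 93% | 82% | 64% |
| 0.005 | 2.80 | 89% | 76% | 58% |
| 0.0072 | 3.58 | 81% | 66% | 49% |
| 0.01 | 4.59 | 71% | 56% | 41% |
| 0.02 | 8.18 | 47% | 35% | 26% |
| 0.05 | 18.95 | 23% | 18% | 14% |

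Power equals 81% at ICC 0.0072 (normal), 0.0041 (6 df) and 0.0015 (3 df). A one-sided test on 6 df moves the limit to 0.0070. On 6 df the effect detectable with 81% power is 0.21 at ICC 0.005, 0.27 at 0.01 and 0.36 at 0.02.

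**Gains that the table leaves out, at ICC 0.01.**
- If region carried half of the between-university variance (assumption), DE = 0.99 + 360 × 0.005 = 2.79, and paired power on 3 df is 58% rather than 41%.
- If adjustment for baseline university means removed 64% of the between-university variance, as a correlation of 0.8 would (assumption), DE = 0.99 + 360 × 0.01 × 0.36 = 2.29, and power on 5 df is about 81% rather than 56%.

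**The case against.** The best defence is that the section fixes neither the effect-size metric nor the base rate. A 20% relative reduction from a base rate near 20.5% gives 81.0% with the stated numbers, and the planning survey's rate cannot be seen here. A journal article may also leave the ICC and design effect to the full protocol, and a design effect of about 3.6 would make the figure correct under normal theory. The 6-df table is one analysis among several: allocation is within region, and the Quantitative analysis section compares use before and after the intervention, so pairing or baseline adjustment may recover power.

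Much of this stands. A reader might infer that the authors made an arithmetic error. The document does not show that, because the metric and any clustering allowance are unreported; it shows only that the figure cannot be derived from what is printed. A reader might also infer that the trial has about half the claimed power. That needs an ICC of about 0.016 on 6 df, or about 0.010 on 3 df with no benefit from pairing, and no ICC is given.

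The defence does not rescue the 81% itself. The risk-ratio and odds-ratio readings leave nothing for clustering, in a trial that allocates universities. The design-effect reading gives 66% once the reference distribution reflects eight universities without pairing or adjustment. The unadjusted table is a fair match to the section's own description of a comparison at follow-up, but it should be read as a lower-end scenario.

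**Conclusion.** The 81% is unsupported as printed. For a standardised 0.2, the stated inputs give over 99.9% if clustering is ignored. If clustering is included with four universities per arm, an unadjusted two-sided comparison of follow-up rates on 6 df reaches 81% only at an ICC of about 0.004 or less.

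The size of any shortfall is conditional. At an ICC of 0.005 the power, 76%, is close to the claim; at 0.01 it is 56% and at 0.02 it is 35%. The limit of 0.004 belongs to that one test. It is 0.0072 under normal theory, 0.0015 on 3 df with no credit for pairing, and would differ again with baseline adjustment.

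These results assume 0.2 is d or h, equal clusters of 360 completers and the ICCs shown. The 62% heavy-drinking prevalence in the Background comes from a different cited source than the planning survey, so it cannot stand in for the missing base rate.

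**What to change.** Withdraw the 81%, or restate it in a rewritten Sample size paragraph that gives:

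- the effect-size metric, the base rate of heavy drinking from the planning survey, and the two rates that the effect implies;
- whether the test is one- or two-sided;
- an ICC range, with power and detectable difference across it, for four against four universities of 360 completers;
- a t reference distribution whose degrees of freedom match the planned analysis, crediting regional pairing or baseline adjustment only if that analysis uses them.

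The baseline survey, which precedes the feedback, may inform the ICC range. Eight universities estimate an ICC too imprecisely for it to fix a single value. The restated figures should be settled before follow-up data are seen.

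The cost is one paragraph and a short calculation. Recruitment, endpoint and schedule are unchanged. The stated power will probably be less favourable.

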### Design of the baseline questionnaire

We will employ a web-based survey. The advantage of a web-based survey is that it is anonymous and that the questionnaire can be personalized to students’ gender and university. University students are a computer-literate population. A web-based survey is therefore a reliable survey tool [27]. Baseline and follow-up questionnaires will be identical for both, intervention and delayed intervention control universities. The questionnaires will include items assessing socio-demographic information, such as age, migration background, if applicable, length of stay in the respective country, whether a student came to study to the respective country, religion and importance of religion, place of residence, disposable weekly income, disposable weekly income spent on licit and illicit substances. Furthermore, information on subject and year of study will be assessed.

Students will be asked to answer questions regarding their personal and perceived substance use of peers and their personal attitude and their perceptions of the attitudes of their peers towards using the following substances: Alcoholic beverages, tobacco products, waterpipe, cannabis, non-prescribed medications to improve academic performance, non-prescribed sedatives or sleeping pills, synthetic cannabis, cocaine, ecstasy, other amphetamine-type stimulants, hallucinogens, and inhalants. Licit and illicit substances will be followed by a list of examples and, if applicable, trade or street names for each substance. Regarding alcohol use, the following variables will be assessed: Average and maximum number of alcoholic drinks consumed on a day that alcohol is consumed, number of occasions where students drink until they feel drunk. Along with the items on alcohol use, participants will be provided with a definition of an alcoholic drink as 0.33 liter beer, a small bottle of a ready to drink beverage (0.275 l), a small cocktail (0.2 l, containing 4 cl alcohol), a glass of wine/sparkling wine (0.125 l), and a shot of spirits (0.4 l). Furthermore, two types of polydrug use will be assessed (i.e., simultaneous use of alcohol and tobacco, alcohol and illicit substances, such as cannabis, ecstasy or cocaine).

Referring to this range of substances, students will be asked to report their personal substance use behaviors and attitudes towards substance use and the perceived gender-specific behaviors (*descriptive norm*) and attitudes (*injunctive norm*) of their peers.

Apart from these questions, an adapted version of the CORE Alcohol and Drug Survey Long Form [28] will be used to assess negative consequences of using alcohol or illicit substances (e.g., missing a class or another commitment, unprotected sex, engagement in violent acts). Finally, students will be asked how they heard about the survey (e.g., via email, information during a lecture, social media channel). This will contribute to an improvement in the selection of suitable recruitment channels in future surveys targeting university students. All questions will be referring to a time period of three months prior to assessment. After completing the questionnaire, students will receive the contact information of the researcher who coordinates the study and who can be contacted for project-related questions. Furthermore, they will be informed about local drug counselling services (at their university and available outside the university setting) that can be contacted if they require counselling regarding their personal substance use behavior.

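### The drink definition to be shown to participants counts 0.4 l of spirits as one drink, about ten times out of line with the other listed drinks

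*Protocol article*

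**What the plan says.** The Protocol article, section Design of the baseline questionnaire, states: "Along with the items on alcohol use, participants will be provided with a definition of an alcoholic drink". Five entries each count as one drink:

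- beer: "definition of an alcoholic drink as 0.33 liter beer"
- ready-to-drink: "a small bottle of a ready to drink beverage (0.275 l"
- cocktail: "a small cocktail (0.2 l, containing 4 cl alcohol"
- wine: "a glass of wine/sparkling wine (0.125 l"
- spirits: "a shot of spirits (0.4 l"

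Two of the alcohol items are counted in this unit: "Average and maximum number of alcoholic drinks consumed on a day that alcohol is consumed". A third, the number of occasions of drinking to the point of feeling drunk, is not. The same section says the questionnaires are identical for intervention and control universities. The section on the follow-up survey says the same items are used again. The section on the web-based social norms approach says the feedback is built from the baseline data.

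**The concern.** A drink definition works only if its entries hold roughly the same amount of alcohol, so that one of any of them adds one to the count. The spirits entry breaks this. Its volume exceeds that of the beer, does not fit the word shot, and is ten times the 4 cl given for the cocktail in the same sentence. No other section gives a different figure.

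This is more than a slip in background text, because the article presents the list as what respondents will see when they report how much they drink. A wrong unit would distort the reported number of drinks at baseline and follow-up. It would also distort any feedback on actual peer drinking that is derived from drink counts, and so could reach the content of the intervention as well as its measurement.

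**Working it through.** **Inputs.** The volumes come from the article. It gives no alcohol strengths, so three sets are assumed:

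- Low: beer 4.5%, ready-to-drink 4%, wine 10%, spirits 35%.
- Mid: beer 5%, ready-to-drink 5%, wine 12%, spirits 40%.
- High: beer 5.5%, ready-to-drink 7%, wine 14%, spirits 40%.

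**Step 1: pure alcohol per listed drink** = volume × strength, in ml. The cocktail's 4 cl is read here as spirits.

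| Entry | Volume (ml) | Low | Mid | High |
|---|---|---|---|---|
| Beer | 330 | 14.85 | 16.5 | 18.15 |
| Ready-to-drink | 275 | 11.0 | 13.75 | 19.25 |
| Cocktail (40 ml spirits) | 200 | 14.0 | 16.0 | 16.0 |
| Wine | 125 | 12.5 | 15.0 | 17.5 |
| Mean of these four | – | 13.09 | 15.31 | 17.73 |
| Spirits as printed | 400 | 140 | 160 | 160 |
| Ratio to the mean | – | 10.7 | 10.4 | 9.0 |

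At mid strengths the separate ratios are 160/16.5 = 9.7 (beer), 160/13.75 = 11.6 (ready-to-drink), 160/16 = 10.0 (cocktail) and 160/15 = 10.7 (wine).

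**Step 2: sensitivity to strength.** Take wider ranges: beer 4–6%, ready-to-drink 4–7%, wine 9–14%, spirits 32–40%. The ratio to a single one of beer, ready-to-drink or wine then runs from 128/19.8 = 6.5 to 160/11 = 14.5.

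**Step 3: the other reading of the cocktail.** If 4 cl means pure alcohol, the cocktail holds 40 ml. The spirits entry is then 140/40 = 3.5 to 160/40 = 4.0 times the cocktail. The ratios to beer, ready-to-drink and wine do not change.

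**Step 4: can any strength rescue 0.4 l?** To match the other entries at mid strengths (13.75 to 16.5 ml), the liquid would need a strength of 13.75/400 = 3.4% to 16.5/400 = 4.1%. That is not spirits.

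**Step 5: effect on the total count if the definition is applied literally.** Let f be the share of true intake, in drinks, that comes from spirits, and take a factor of 10.5. The counted share of the true total is (1 − f) + f/10.5:

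- f = 10%: 0.90 + 0.0095 = 0.91
- f = 25%: 0.75 + 0.0238 = 0.77
- f = 50%: 0.50 + 0.0476 = 0.55
- f = 100%: 1/10.5 = 0.095

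**Step 6: does 0.04 l restore consistency?** Forty ml of spirits hold 14, 16 and 16 ml of pure alcohol. Divided by the means in step 1, this gives 1.07, 1.04 and 0.90. The list is then consistent to within about 10%.

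**The case against.** A reader might infer from the printed figure that spirits drinking will be under-counted tenfold. The article does not support that as a fact. It describes the questionnaire and does not reproduce it, so a misplaced decimal in the article alone explains the text equally well. The entry is also called a shot, and many students would count each shot as one drink whatever volume stood beside it. Even under literal use, the factor applies to the spirits part of intake only.

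Other extensions are also tempting and fall short:

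- *All alcohol outcomes are affected.* The drunkenness item does not use the unit. The article gives no heavy-drinking cut-off and does not say that heavy drinking is derived from drink counts, so misclassification of heavy drinkers cannot be shown or sized.
- *The sample size is affected.* "The sample size calculation is based on the prevalence for heavy drinking reported in a previous study conducted in Germany with 3307 students". Nothing shows that the earlier study used this drink definition.
- *The comparison between arms is biased.* The questionnaires are identical at intervention and control universities, so a wrong unit would act alike in both.
- *The feedback would show too low an actual norm against an unchanged perceived norm.* Perceived peer use is asked in the same survey and would plausibly share the unit, so both could shift. The article also does not say which alcohol measures the feedback displays.

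These points limit the consequence. They leave the inconsistency standing: the figure is printed, it fits no plausible strength, and nothing corrects it.

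**Conclusion.** The point holds as an internal inconsistency in a measuring unit. The spirits entry is out of line with the other listed drinks by about a factor of ten. That size rests on assumed strengths, but the wider ranges tried still leave it at least 6.5 times beer, ready-to-drink or wine.

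The harm is conditional. It needs the fielded form to show 0.4 l and students to follow it literally. In that case the average and maximum drinks items, and any feedback drawn from them, would understate drinking in proportion to the spirits share. If only some students follow it, respondents would be counting in different units and the items would become noisier. Whether either has happened cannot be told from the article.

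**What to change.** In the drink definition, replace the spirits volume with one equivalent to the other entries. A volume of 0.04 l (4 cl) matches the cocktail entry and makes the list consistent. State also whether the cocktail's 4 cl is spirits or pure alcohol.

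Then check that the programmed baseline and follow-up questionnaires, and any feedback page that repeats the definition, show the corrected figure. Before launch this costs one figure in the text and a look at the web form. If the baseline has already been collected, the report should state which volume students saw, because correcting the follow-up alone would change the unit between the two surveys.
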